## Abstract

**Background:**

Out-of-hospital cardiac arrest (OHCA) is a major health concern in Europe, leading to significant morbidity and mortality. Survivors often suffer from cognitive deficits, anxiety, and depression, that affect significantly their quality of life. Current post-discharge care is inconsistent and frequently overlooks subtle but disabling symptoms. The ENFORCER trial aims to significantly enhance the health and quality of life of OHCA survivors by providing a comprehensive, accessible, and user-friendly internet-based lifestyle intervention.

**Methods:**

ENFORCER is a multicentre, parallel group randomized controlled trial involving OHCA survivors aged 18–80 years with cognitive impairment or anxiety/depression measured through validated instruments.

Participants will be randomized 1:1 to the intervention or the control group. The intervention group will receive a one-year program via a secure web application, offering cognitive, emotional, and physical rehabilitation support. The control group will receive standard care.

The primary outcome is the difference in the proportion of patients without cognitive or emotional symptoms between the two groups after one year.

Secondary outcomes include changes in the level of patients’ cognitive and emotional symptoms, quality of life, sleep quality, sexual interest and satisfaction, and caregivers’ burden, quality of life, sleep quality and emotional symptoms in the two groups.

**Discussion:**

The trial addresses the need for consistent post-discharge care, and the timely detection and treatment of cognitive and emotional problems. The internet-based approach allows to potentially reach many patients, ensuring cost-effectiveness and high adherence rates.

The study results could establish a standard for post-OHCA care, improving long-term recovery and quality of life for survivors.

Trial registration.

The trial is registered at clinicaltrials.gov (NCT06395558).

## Introduction

Out-of-hospital Cardiac Arrest (OHCA) significantly contributes to morbidity and mortality in Europe, with rates ranging from 67 to 170 per 100,000 people and an average 8% survival rate after hospital discharge. Approximately half of the survivors experience adverse neurological outcomes.^1^

Recent studies over the past two decades have shown that a significant number of those who survive with favourable neurological statuses, typically classified as Cerebral Performance Category (CPC) 1 or 2, are affected by persistent cognitive deficits, as well as anxiety and depression, which consequently impair their health-related quality of life (HRQoL).^2^, ^3^

Current guidelines from the European Resuscitation Council (ERC) recommend that OHCA survivors be followed up for within three months of discharge to identify and address any psychological or cognitive problems, thereby providing support to both patients and caregivers.^4^

In Italy, the likelihood of surviving OHCA with a positive neurological prognosis is consistent with European data.^5^. However, post-discharge care lacks a consistent approach to assessing cognitive or emotional problems, with follow-up care typically managed by specialists treating the underlying condition responsible for the OHCA (for instance, cardiologists), or in other cases, referring patients back to their primary care physicians. As a result, subtle symptoms may go unrecognized or untreated.

Lifestyle interventions are one possible strategy to support changes in physical and mental health by promoting improvements in cognitive and emotional functioning, physical activity and diet. Such interventions include a variety of programs that include the provision of health education, and cognitive-behavioural therapy (CBT), and may also include practical components such as participation in physical activity or mental exercises.^6^

The implementation of these strategies has been successful in alleviating symptoms in individuals suffering from anxiety and depression,^6^, ^7^, ^8^ and has also been beneficial in improving mild cognitive impairment.^9^ In addition, the use of an internet-based approach to these interventions allows a significant number of patients to be reached while maintaining cost-effectiveness.

In the existing literature, several online projects that have been developed to identify and improve psychological problems through lifestyle changes.^10^, ^11^ Furthermore, these online interventions have shown levels of adherence and effectiveness comparable to traditional treatments that involve a face-to-face approach.^12^, ^13^, ^14^

Nevertheless, there is a lack of specific internet-based lifestyle intervention programs tailored for individuals who have survived OHCA.

ENFORCER (intErnet-based iNterventions FOR Cardiac arrEst suRvivors) is a multicentre randomized controlled interventional trial exploring the effectiveness of a web-based lifestyle intervention on anxiety, depression and cognitive symptoms in cardiac arrest survivors.

## Protocol

The study protocol was drafted according to the SPIRIT (Standard Protocol Items: Recommendations for Interventional Trial) guidelines^15^ and will be reported following the CONSORT (Consolidated Standards of Reporting Trials) guidelines,^16^ together with the CONSORT-EHEALTH extension.^17^

The trial was approved on March 14th, 2024, by the local ethics committee of the sponsor and all participating institutions involved in patient enrolment or treatment (registration number: 74–2024-SPER-AUSLBO). It is registered on clinicaltrials.gov (NCT06395558). The Local Health Authority of Bologna is the sponsor and promoter of the trial, which is funded by a research grant from Fondazione Italian Resuscitation Council ETS (FIRCBRS23-001), a not-for-profit organization dedicated to supporting cardiac arrest survivors and their families (https://www.fondazioneirc.org).

### Aims

The primary aim is to evaluate the effectiveness of internet-based lifestyle interventions on anxiety, depression and cognitive impairment in OHCA survivors with good neurological recovery compared to usual care. The primary outcome is the difference in the proportion of patients without cognitive or emotional symptoms between the two groups one year after enrolment.

The first secondary aim is to evaluate the effectiveness of internet-based lifestyle interventions on HRQoL, behavioural efficiency, and sleep quality in OHCA survivors with good neurological recovery. Outcomes will be assessed at baseline and at 1-, 3-, 6-, and 12-months post-randomization with continuous log-data collection for user engagement.

Other secondary aims include the assessment of caregivers’ HRQoL, anxiety and depression, sleep quality and burden, the validation of the Italian version of the Sexual Interest and Satisfaction Scale (SISS) and the identification of factors associated with anxiety and depression in OHCA survivors with good neurological recovery.

Primary and secondary objectives and outcome measures are listed in Table 1.

**Table 1 t0005:** Outcomes and Outcome Measures of the ENFORCER study.

Outcome	Outcome measure
Primary endpoint	
Effectiveness of internet-based lifestyle interventions on anxiety, depression and cognitive impairment	Proportion of patients without cognitive or emotional symptoms (HADS<8 and TICS>31) one year after enrolment
Secondary endpoints	
Effectiveness of internet-based lifestyle interventions on patients’ health-related quality of life, sleep quality, behavioral efficiency, sexual function, and on caregivers’ burden, health-related quality of life, sleep quality and emotional symptoms	Short Form Health Survey 12 (SF-12) Pittsburgh Sleep Quality Index (PSQI) Neurobehavioral rating scale (NRS) Patient Competency Rating Scale (PCRS) Sexual Interest and Satisfaction Scale (SISS) Zarit Burden Inventory (ZBI)
Factors associated with emotional or cognitive impairment	Presence or absence of the cognitive or emotional symptoms at enrollment (t_-1_)
Italian validation of the Sexual Interest and Satisfaction Scale	−

Abbreviations: HADS – hospital anxiety and depression scale; TICS – telephone interview for cognitive status.

### Study design and setting

ENFORCER is an interventional parallel-group randomized controlled trial. Recruited participants will be randomized 1:1 to the intervention or control group using simple computerized randomization obtained at the time of enrolment.

The 38 collaborating institutions will refer potentially eligible patients to the coordinating centre for participation, but also caregivers and self-referral are allowed.

All outpatients who meet the eligibility criteria will be recruited after discharge from hospital, regardless of geographic location.

A trained neuropsychologist, blinded to patient group allocation, will conduct the clinical assessments. All professionals involved in data management and analysis will also be blinded to group allocation. Unblinding will be possible only at the request of the Data Safety and Monitoring Board (DSMB).

### Eligibility criteria

OHCA survivors within 15 days of hospital discharge will be considered eligible for randomization. Inclusion criteria will be age 18–80, no history of severe mental or neurological illness, a good neurological outcome (CPC 1–2) at hospital discharge, Hospital Anxiety and Depression Scale – HADS^18^ score ≥ 8 and/or cognitive impairment (Telephone Interview for Cognitive Status^19^ – TICS score ≤ 31.

Italian language skills and Internet literacy will be required to ensure compliance with treatment and interviews. Prior to enrolment, patients will be asked to give their consent to participate in the study and to have their personal data processed, after an explanation of the study objectives and procedures and an opportunity to ask questions.

Survivors experiencing anxiety, depression, or cognitive impairment will be randomly assigned to the intervention or the control group. For each survivor recruited, a caregiver will also be included in the study, and given access to a parallel account on the web application.

Individuals who do not meet the criteria for anxiety, depression, or cognitive impairment will not be included in the trial and allocated to the treatment groups. However, baseline information will be collected for the secondary analysis to identify factors associated with these conditions after hospital discharge.

### Planned visits

In this study all scheduled visits will be conducted via video web calls to gather data on instruments needing clinician ratings, while self-report questionnaires will be filled out using a web application.

The study procedures are shown in Fig. 1. OHCA survivors who leave the hospital or rehabilitation institute with a good neurological outcome are screened within 15 days of discharge. (visit t-_1_).

**Fig. 1 f0005:**
[figure not shown]
Patients’ flow through the study. Abbreviations: HADS – Hospital Anxiety and Depression Scale, TICS – Telephone Interview for Cognitive Status. Notes: patients not fulfilling the inclusion criteria for HADS or TICS will have their data kept for secondary analyses of the factors associated with anxiety and depression in OHCA survivors with good neurological recovery.

Web-based follow-up assessments and self-administered questionnaires are scheduled at 1, 3, 6, and 12 months after randomization. The video web-based face-to-face assessments will focus on those instruments requiring clinical evaluations and monitoring any changes in therapy or hospital admissions. The timeline for participants is shown in Table 2.

**Table 2 t0010:** Schedule of enrolment, interventions, and assessments.

Notes: t_-1_ – 0–––14 days from hospital discharge; t_1_ – 1 month post enrolment; t_2_ – 3 months post enrolment; t_3_ – 6 months post enrolment; t_4_ – 12 months post enrolment.

Adherence and intensity of the treatment will be monitored through the number of accesses and the total time spent on the web app. Weekly diaries tracking physical activity (using the Godin Leisure Time Exercise),^20^ social activities, will also be collected. Baseline data, adherence to intervention and safety-related variables are listed in Table 3.

**Table 3 t0015:** Data collected and indicators of safety and adherence.

OHCA event and hospital stay-related variables
Age
Sex
Comorbidities
Cause of cardiac arrest
Onset rhythm
Bystander CPR
No flow and low flow time
Presence of STEMI
Targeted Temperature Management
ECMO
Length of ICU stay
Length of hospital stay
Level of education
Employment status before the event
Marital status
Employment status after the event
Weekly diaries
Weekly diaries related to sleep quality, social life, and physical activity
Safety indicators
Number of hospitalizations and their causes during the study period
Death during the study period
Ongoing medications (Sedatives, antidepressants, antipsychotics, opiates, other analgesics)
Ongoing physical therapy
Ongoing psychological therapy
Adherence indicators
Number of accesses to the site
Hours spent on the site
Number of re-readings of information material
Number of exercises completed

Abbreviations: OHCA – out-of-hospital cardiac arrest; CPR – cardiopulmonary resuscitation; STEMI – ST-elevated myocardial infarction; ECMO – Extracorporeal Membrane Oxygenation, ICU – intensive care unit.

The study will utilize several instruments to assess various aspects of patient health and caregiver burden.

These include the HADS and TICS for anxiety, depression, and cognitive impairment;^18^, ^19^ the Short Form 12 (SF-12) for HRQoL;^21^ the Pittsburgh Sleep Quality Index (PSQI) for sleep quality;^22^; the Patient Competency Rating Scale (PCRS) for self-awareness post-brain injury;^23^ and the Neurobehavioral Rating Scale (NRS) for cognitive and noncognitive symptoms.^24^

The SISS,^25^ used for assessing sexual desire and interest post-trauma, will be validated in Italian in this study.

Caregiver HRQoL, anxiety, depression and sleep quality will also be measured using the SF-12, the HADS and the PSQI. Finally, the Zarit Burden Inventory (ZBI)^26^ will be used to assess the impact of the patient’s disability on the caregiver’s daily life.

More details on these instruments are reported in Table 4.

**Table 4 t0020:** Outcome measures.

Instrument	Description
Hospital Anxiety and Depression Scale (HADS)	14-item self-report scale used to measure anxiety and depression in patients and caregivers.. A cut-off score < 8 is used to denote the presence of the primary outcome^18^
Telephone Interview for Cognitive Status (TICS)	11-item observer-rated instrument used for cognitive impairment. The cut-off score > 31 is used to denote the presence of the primary outcome^19^
Short-Form 12 (SF-12)	12-item self-report scale used to measure the Health-Related Quality of Life in patients and caregivers. It is an instrument of widespread use in clinical and non-clinical contexts^21^
Pittsburgh Sleep Quality Index (PSQI)	19-item self-report instrument that proved to be a useful, valid and reliable tool for assessing sleep quality.^22^ It is administered to patients and caregivers.
Patient Competency Rating Scale (PCRS)	30-item self-report instrument which asks the subject to rate his or her degree of difficulty in a variety of tasks and functions on a 5-point Likert scale.^23^
Neurobehavioral Rating Scale (NRS)	29-item observer-rated instrument measuring a broad range of cognitive and noncognitive symptoms. It is a structured interview targeting behavioural and cognitive concerns and symptoms, in which the clinician evaluates responses and integrates observational data to characterize the patient’s level of neurobehavioral functioning.^24^
Sexual Interest and Satisfaction Scale (SISS)	6-item self-report scale measuring sexual desire and interest before and after a traumatic event, originally developed for patients affected by spinal cord injury.^25^
Zarit Burden Inventory (ZBI)	A self-report questionnaire of 22-items used to evaluate the burden of care on the caregiver. Its items investigate how a patient’s disability impacts the caregiver’s quality of life, psychological distress, guilt, financial problems, shame, and social and family difficulties.^26^

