### Control group

Patients randomized to the control group will be followed up by their primary care physician (usual care). They will be asked to complete the diaries and all the assessments at the same scheduled follow-up visits and as the intervention group.

Throughout the study, participants will be allowed to receive concurrent pharmacological, psychological, or physical treatments. The concurrent use of medications such as antidepressants, anxiolytics, antipsychotics, opiates, and other analgesics, as well as any form of psychotherapy or physiotherapy, will be carefully recorded at the scheduled visits.

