### Data collection and statistical analysis plan

Questionnaires and diaries completed by participants will be collected directly via an electronic case report form (eCRF) integrated into a web application. The same application will facilitate data entry for the researcher conducting the observer-rated assessments, using a distinct user interface with unique login credentials. To ensure data quality, the rater will be trained in clinical assessment and completion of the observer-rated questionnaires. Participants will be automatically checked for data completeness, and they will receive regular reminders to ensure timely data entry.

The proportions of patients without cognitive or emotional symptoms 12 months after enrolment will be compared between groups using the z-test. A modified intent-to-treat approach will be used, including in the analysis patients who received at least one the web-based treatment session or standard care. To manage missing/incomplete data and to address a possible selection bias related to the modified intent-to-treat approach we will focus on the possible distribution of the missing data given the observed data. In order to do so, we will determine whether the distribution of patients’ unseen observations at the final visit, given their observations at previous visits and baseline, is different from that seen among the patients who have no missing data. To estimate the intervention effect at the end of the trial, we will make assumptions about how the patterns differ in the two groups of patients. We will then estimate the intervention effect amongst those who do, and do not have, missing data, which has to be averaged, to arrive at the overall estimate of the effect of intervention.^29^

Secondary outcome measures will be compared between the two groups using the *t*-test or Mann-Whitney *U* test according to their frequency distribution.

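### Therapy and admission questions share the video call with the blinded-rated TICS and NRS and may reveal the arm; collect the therapy items by self-report hidden from the rater, since reordering alone only reduces the risk

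*Protocol article*

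**What the plan says.** All references are to the protocol article.

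- **Study design and setting:** "A trained neuropsychologist, blinded to patient group allocation, will conduct the clinical assessments".
- **Planned visits:** all visits are video calls for the clinician-rated instruments, while "self-report questionnaires will be filled out using a web application". The text after Figure 1 gives the content of the calls: "instruments requiring clinical evaluations and monitoring any changes in therapy or hospital admissions". They take place at months 1, 3, 6 and 12.
- **Table 4:** TICS is an "11-item observer-rated instrument used for cognitive impairment", and NRS is a "29-item observer-rated instrument measuring a broad range of cognitive and noncognitive symptoms". HADS is self-reported.
- **Table 1:** the primary endpoint requires HADS<8 and TICS>31 at one year.
- **Table 3:** ongoing medication, physical therapy and psychological therapy are among the data to be collected, as are hospitalizations.
- **Control group:** concurrent drugs, psychotherapy and physiotherapy "will be carefully recorded at the scheduled visits".
- **Data collection and statistical analysis plan:** "Questionnaires and diaries completed by participants will be collected directly via an electronic case report form", which is built into the web application. The researcher who does the observer-rated assessments enters data through a separate interface with its own login.

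**The concern.** The intervention consists of cognitive training, emotional support and physical exercise. Participants know whether they have it. A question about what psychological or physical therapy someone is receiving falls in the same categories as the programme, so an intervention participant may answer by describing the web exercises. If the person asking is also the person scoring TICS and NRS, the rater may learn the arm.

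HADS is self-reported by participants who are not blinded, so TICS is the only component of the primary endpoint that rater blinding can protect. NRS, a secondary outcome, relies on the clinician's judgement and is exposed in the same way. A rater who knows the arm may, without intending to, score in favour of the intervention.

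**Working it through.** **1. Do the tasks coincide?** The design section gives the clinical assessments to a blinded neuropsychologist. The planned-visits text puts the clinician-rated instruments and the monitoring of therapy and admissions in the same video assessments. The control-group section records concurrent therapies at the same visits. The data-collection section speaks of the rater in the singular, and no second interviewer appears anywhere. That the rater asks the therapy questions is therefore the natural inference, but it is not stated.

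**2. Are the items arm-specific?** No. Concurrent treatments are allowed, and controls attend the same visits and complete the same diaries. A new drug, a course of physiotherapy or an admission does not identify the arm. The leak needs a participant to volunteer details of the programme.

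**3. How far does reordering help?** The plan gives no figure here. Let u be the chance that an intervention participant discloses the arm in one call. Assume that u is constant, calls are independent and the rater is the same throughout. The chance that the rater knows the arm when scoring the month-12 TICS is:

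- therapy questions before scoring (worst case, as the article gives no order): 1 − (1 − u)^4
- therapy questions after scoring: 1 − (1 − u)^3, because the calls at months 1, 3 and 6 still count

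| u (assumed) | Before scoring | After scoring |
|---|---|---|
| 2% | 7.8% | 5.9% |
| 5% | 18.5% | 14.3% |
| 10% | 34.4% | 27.1% |
| 20% | 59.0% | 48.8% |

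At u = 10%: 1 − 0.9^4 = 0.344 and 1 − 0.9^3 = 0.271. Reordering removes only about a fifth of the cumulative risk, (34.4 − 27.1)/34.4 = 21%.

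**4. What could this do to the primary outcome?** All inputs in this step are assumptions, except the 25-point effect (55% vs 30%) from the sample size section.

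- Assume TICS is roughly normal at 12 months, with mean m from 31.5 to 33.5, SD s from 3 to 4, and a cut at 31.5 for scores above 31. Assume a scoring drift d of 0.5 to 1 point in favour of the intervention.
- Share crossing the cut-off: Φ((m + d − 31.5)/s) − Φ((m − 31.5)/s).
  - Largest (m = 31.5, s = 3, d = 1): Φ(0.333) − Φ(0) = 0.131.
  - Smallest (m = 33.5, s = 4, d = 0.5): Φ(0.625) − Φ(0.5) = 0.043.
- Assume that 60% meet HADS<8, independently of TICS. The shift in the composite is 0.6 × 0.043 = 0.026 to 0.6 × 0.131 = 0.078, or about 3 to 8 points. This applies the drift to every intervention patient, so it is an upper bound under these inputs.
- Scale by the share unblinded, taken from step 3 at u = 5% and u = 10%: 2.6 × 0.185 = 0.5 points and 7.8 × 0.344 = 2.7 points. Against the 25-point effect, this is 0.5/25 = 2% to 2.7/25 = 11%.

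**The case against.** The strongest reply is that this is a matter of operational detail. Question order, form locking, a non-disclosure script and a guess of the arm commonly sit in a full protocol or a manual, and the full protocol is not shown. The article says that the rater is blinded and nowhere contradicts it. It never says that the rater personally asks the therapy questions. The items do not mark the arm, and a participant could as easily mention the programme during the NRS interview, which has to stay in the call.

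Much of this stands. The absence of a stated order or script is no fault in an article, and a reader might infer that blinding is contradicted or already lost, which the documents do not show. What remains is a stated choice: the article itself places therapy monitoring in the calls that carry the observer-rated instruments. That the NRS interview may also prompt disclosure is no reason to add a more direct prompt.

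The reply is also right on completeness. Hospitalizations are a main outcome monitored by the DSMB (Monitoring section), and some participants will have cognitive impairment, so self-report could lose safety data.

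**Conclusion.** The point holds as a plausible and avoidable risk to the blinding of TICS and NRS. It rests on the inference that the rater asks the therapy questions.

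Three stronger readings are tempting and should not be adopted:

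- **That reordering the call solves the problem.** It protects only the score given in that call. With one rater, what is learned at months 1, 3 or 6 is still known at month 12.
- **That the primary outcome would move by 3 to 8 points.** That figure requires every intervention patient to be unblinded. With 18.5% to 34.4% unblinded, the same assumptions give about 0.5 to 2.7 points. The documents supply none of the TICS mean, SD, drift, HADS share or disclosure rate, so neither range is an estimate for this trial.
- **That the change would protect the whole primary endpoint.** HADS stays self-reported by unblinded participants whatever is done here.

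The case for acting rests on inexpensive support for the blinding claim, not on the size of the shift. It is worth changing but does not undermine the trial.

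**What to change.** 1. Collect therapy changes and concurrent treatments through the participant's existing form in the web application. Hide the answers, including any free text, from the rater's interface. This removes the direct prompt from all four calls, though not spontaneous disclosure.
2. Where any such questions stay in the call, admissions included, open them only after TICS and NRS have been scored and locked in the eCRF.
3. Begin each call with a scripted request not to mention the programme.
4. Have the rater record a guess of the arm once the month-12 TICS is locked, and report it.

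**Cost:** a change to the form layout and access rights, and a short visit script, with no additional visit. Whether it needs no additional staff cannot be confirmed, because the article gives no staffing data. The main downside is somewhat less complete reporting. This matters most for admissions as a DSMB safety outcome, so completeness of these forms must be checked, preferably by someone other than the rater.
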